## Abstract

**Background:**

Between 30 and 40 % of patients with severe injuries receive treatment at non-trauma centers (under-triage), largely because of physician decision making. Existing interventions to improve triage by physicians ignore the role that intuition (heuristics) plays in these decisions. One such heuristic is to form an initial impression based on representativeness (how typical does a patient appear of one with severe injuries). We created a video game (*Night Shift)* to recalibrate physician’s representativeness heuristic in trauma triage.

**Methods:**

We developed *Night Shift* in collaboration with emergency medicine physicians, trauma surgeons, behavioral scientists, and game designers. Players take on the persona of Andy Jordan, an emergency medicine physician, who accepts a new job in a small town. Through a series of cases that go awry, they gain experience with the contextual cues that distinguish patients with minor and severe injuries (based on the theory of analogical encoding) and receive emotionally-laden feedback on their performance (based on the theory of narrative engagement). The planned study will compare the effect of *Night Shift* with that of an educational program on physician triage decisions and on physician heuristics. Psychological theory predicts that cognitive load increases reliance on heuristics, thereby increasing the under-triage rate when heuristics are poorly calibrated. We will randomize physicians (*n* = 366) either to play the game or to review an educational program, and will assess performance using a validated virtual simulation. The validated simulation includes both control and cognitive load conditions. We will compare rates of under-triage after exposure to the two interventions (primary outcome) and will compare the effect of cognitive load on physicians’ under-triage rates (secondary outcome). We hypothesize that: a) physicians exposed to *Night Shift* will have lower rates of under-triage compared to those exposed to the educational program, and b) cognitive load will not degrade triage performance among physicians exposed to *Night Shift* as much as it will among those exposed to the educational program.

**Discussion:**

Serious games offer a new approach to the problem of poorly-calibrated heuristics in trauma triage. The results of this trial will contribute to the understanding of physician quality improvement and the efficacy of video games as behavioral interventions.

**Trial registration:**

clinicaltrials.gov; NCT02857348; August 2, 2016.

## Background

Treatment at trauma centers improves outcomes for patients with moderate-to-severe injuries [1–3]. Professional organizations, state authorities, and the federal government endorse the systematic triage and transfer of these patients to trauma centers either directly from the field or after evaluation at a non-trauma center [4]. Nonetheless, between 30 and 40 % of patients with moderate-to-severe injuries still receive treatment at non-trauma centers (*under-triage)* [5–7]. The problem amplifies among the cohort evaluated by physicians at non-trauma centers—70 to 80 % of whom are under-triaged [8, 9].

Current efforts to change physician decision making in trauma triage focus primarily on education and outreach by opinion leaders [10]. These strategies assume that the problem is one of ignorance. In other words, physicians make the wrong decision because they either lack knowledge of the clinical practice guidelines or do not believe in the validity of the guidelines. However, this approach ignores the influence of intuitive judgments (*heuristics*) on triage decisions. Heuristics, mental short cuts based on pattern recognition, drive most decision making. They take precedence over rule-based algorithms (analytic cognitive processes), by springing to mind spontaneously and effortlessly. They work well under conditions of time-pressure and uncertainty precisely because they ignore irrelevant information and streamline decision making. Most importantly, they generate useful answers most of the time. However, they can also draw attention to the wrong contextual cues, leading to predictable errors of judgment (*biases*) [11–13]. Our observational and experimental work suggests that the use of heuristics may explain some patterns of non-compliance with clinical practice guidelines in trauma triage [14–16].

Because they are automatic, the use of heuristics cannot be eradicated. Moreover, the uncertainty and complexity of the clinical environment make well-calibrated heuristics a powerful tool [17]. We propose what we believe to be the first intervention designed to recalibrate physician heuristics. It draws on research from other domains suggesting the potential effectiveness of promoting *analogical encoding* and *narrative engagement*. Analogical encoding interventions use case studies to highlight core principles of decision making, emphasizing the identification of relevant and irrelevant contextual cues [18–21]. Narrative engagement interventions use messages designed to resonate with recipients in personally relevant and meaningful ways. Our intervention is an adventure video game that combines these two features [22, 23]. The planned study will compare the impact of the game on simulated physician trauma triage decisions with that of an educational program of equivalent duration.

## Methods

### Overview

We developed the video game (*Night Shift*) in collaboration with Schell Games (Pittsburgh, PA) through an iterative process involving behavioral scientists, cognitive psychologists, trauma surgeons, and emergency medicine physicians. We plan to compare the impact of *Night Shift* with that of a standard educational program on simulated triage decisions made by a convenience sample of emergency medicine physicians. We will recruit physicians working at non-trauma centers, randomize them to play *Night Shift* or to review a standard educational program, and assess their decision making on a validated virtual simulation.

The virtual simulation allows us to assess physician performance in terms of the number of severely injured patients not transferred to trauma centers (under-triage). We can also assess the effect of *Night Shift* on physician heuristics, by experimentally manipulating cognitive load in the simulation. Psychological theory predicts that cognitive load will increase reliance on heuristics, thereby increasing the under-triage rate in situations where those heuristics are inaccurate [24]. Our target heuristic is representativeness. In the context of trauma triage, it would entail forming an initial impression based on how typical a patient appears of the severely injured.

We hypothesize that: a) physicians exposed to *Night Shift* will have lower rates of under-triage compared to those exposed to the educational program, and b) cognitive load will not degrade triage performance among physicians exposed to *Night Shift* as much as it will among those exposed to the educational program.

### Participants

#### Study setting

Using a strategy that has proven successful in the past, we will recruit physicians at a national meeting of the American College of Emergency Physicians in the fall of 2016, using a booth in the Exhibition Hall [15, 16]. Physicians will be eligible for participation if they care for adult patients in the Emergency Department of either a non-trauma center or a Level III/IV trauma center in the United States. We will obtain verbal consent from eligible physicians, informing them that the study focuses on evaluating how best to disseminate clinical practice guidelines in trauma.

#### Randomization and blinding

We will randomize eligible physicians to complete (a) either *Night Shift* or the educational intervention, *myATLS and Trauma Life Support MCQ Review,* and (b) either the control or cognitive load version of a virtual simulation [Fig. 1]. We will generate a randomization scheme using Stata 13.0 (Statacorp, College Station, TX, USA) statistical software, using random block sizes of 4 or 8. After registering the participant, study personnel will obtain the intervention assignment from a central database. Although we cannot blind study personnel and participants to the intervention after allocation, we will mask group assignment during the analysis phase.

**Fig. 1 Fig1:**
[figure not shown]
Overview of study protocol. Description of data: Flow diagram of recruitment and allocation strategy

### Study protocol

Upon enrollment, subject physicians receive an iPad mini 2 with their intervention pre-loaded, along with written instructions on how to complete the study protocol. They will receive weekly reminder emails to complete the protocol for the duration of the study. We will ask participants to spend a minimum of one hour completing the intervention task. After completing it, they will be instructed to log in to a website that hosts: a) the virtual simulation; b) a questionnaire about their personal information, and c) a questionnaire about the intervention’s tolerability. Completing the simulation and two questionnaires will take approximately one hour. Participants will be able to complete the two portions of the study protocol at their convenience, within 1 month of enrollment. They will keep the iPad mini 2 as an honorarium (approximate value $260).

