**Fig. 2 Fig2:**
[figure not shown]
Screen shots of trailer to Night Shift. Description of data: We show the trailer to the game. We provided players with two explicit objectives in order to heighten narrative engagement, while simultaneously providing a vehicle for physician education

The patients who present to the ED have both severe injuries and non-trauma complaints. In each case, subject physicians must interview the patients to elicit relevant elements of the history and physical exam. They then have the option of: a) ordering ancillary testing, b) discussing the case with a consultant, or c) discharging the patient home. Cases end when players make disposition decisions (admit, transfer, or discharge).

We categorize cases as ‘relevant’ or ‘non-relevant’ to our objective. ‘Relevant’ patients have non-representative severe injuries. When players fail to transfer one of these patients, he/she returns with complications that require additional treatment. Players also receive feedback on their performance from peers, family members, or their supervisor. The feedback includes both information about the clinical practice guidelines and a personal reprimand. In contrast, when players successfully transfer the patient to a trauma center, they receive an update, stating that the patient has improved, information about the guidelines, and a compliment on their diagnostic and decision-making capability.

‘Non-relevant’ patients either have representative severe injuries or non-trauma complaints. We included these cases because playtesters found that the ‘relevant’ cases did not pose sufficient diagnostic challenge, making game-play tedious. Players do not receive in-game feedback on their treatment of these patients. However, we do provide a summary of their performance at the end of *Night Shift*, which includes their ability to diagnose and treat the ‘non-relevant’ cases.

The mystery component of *Night Shift* occurs concurrently with the clinical challenges, and serves to facilitate players’ identification with their character and interest in their task. Players must solve Robert’s disappearance through interactions with other characters, including patients, and their physical environment. Andy Jordan’s background and character are also revealed through these interaction, which are designed to make him and his decisions more appealing and sympathetic [Table 1].

**Table 1 Tab1:** Description of *Night Shift*

Duration: Three hours of gameplay possible.	

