#### Intervention: educational control

The gold standard educational strategy in trauma is *Advanced Trauma Life Support (ATLS)*. The American College of Surgeons have developed ATLS, a 2-day seminar, to teach participants: to assess the patient’s condition rapidly and accurately; to resuscitate and to stabilize the patient; to determine if the patient’s needs exceeds the capabilities of their facility; to arrange for the definitive care of the patient, and to ensure that optimal care if provided. The course includes lectures on key topics (e.g. assessing the severity of the injury), instruction on skills relevant to the initial stabilization of the patient (e.g. putting in chest tubes), and practice using standardized patients. Participants must complete a multiple choice test before and after the course to receive certification [25].

We will use a two-part educational program as a surrogate. First, physicians review the *myATLS* app, designed and produced by the American College of Surgeons as an adjunct to the ATLS course [26]. The app includes a review of each chapter of the ATLS textbook, a series of videos demonstrating common trauma procedures, and clinical resources including checklists for use at the bedside. Second, physicians use the *Trauma Life Support MCQ Review*, an app designed to help students prepare for the ATLS exam. It includes 550 multiple-choice questions with correct answers and explanations. We will ask physicians to review the *myATLS* app and then complete questions in the *Trauma Life Support MCQ Review*, spending at least 1 h on the combined tasks.

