#### Outcome assessment

After completing their assigned interventions, subjects will log into a website to complete a virtual simulation designed to replicate the task environment of an Emergency Department at a non-trauma center. The primary outcome of the clinical trial will be performance on the simulation, measured as the physician’s rate of under-triage (proportion of severely injured patients not transferred to a trauma center). We previously collaborated with a gaming company (Breakaway Ltd; [name]) to develop a 2-D simulation to assess physician decision making in trauma triage [Fig. 3]. The simulation has both internal reliability as well as construct validity [16]. Most importantly, in prior studies, we found that physicians make similar decisions for trauma patients on the simulation as they do in real-life. Performance on the virtual simulation will be transmitted from the website to a secure server hosted by the University of Pittsburgh.

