### Analyses

We will calculate the response rate as the proportion of enrolled physicians who start to use their assigned intervention, and the completion rate as the proportion who finish the virtual simulation. We will include physicians in the analysis who do not spend one hour on their assigned intervention (i.e. evaluating it in terms of intention-to-treat). We will exclude physicians who do not complete the virtual simulation (i.e., those for whom we have missing outcome data).

We will summarize physician characteristics (including personality traits) using means (standard deviations) for continuous variables and proportions (%) for categorical variables, and will compare the distribution of characteristics between the two intervention groups using Students *t*-test and chi-squares as appropriate.

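### The primary-outcome simulation is sequenced after completing the intervention, at a self-chosen date, so physicians who abandon the app are more likely to lack an outcome and the exposure-to-test interval is uncontrolled

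*Protocol article*

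**What the plan says.** Under Study protocol, each physician receives a tablet with the assigned app and written instructions at enrolment, then weekly reminder emails. On the intervention: "We will ask participants to spend a minimum of one hour completing the intervention task". The next step is: "After completing it, they will be instructed to log in to a website that hosts: a) the virtual simulation". Outcome assessment repeats the order: "After completing their assigned interventions, subjects will log into a website to complete a virtual simulation". The only timing rule is: "Participants will be able to complete the two portions of the study protocol at their convenience, within 1 month of enrollment". No assessment day and no interval between last exposure and test is set.

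The Analyses section states: "We will include physicians in the analysis who do not spend one hour on their assigned intervention", and calls this intention-to-treat. It then removes physicians who do not complete the simulation. It also defines two rates: response (starting the assigned intervention) and completion (finishing the simulation).

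On the two tasks, Table 1 says of the game: "Duration: Three hours of gameplay possible". Of the control question app, the article says: "It includes 550 multiple-choice questions with correct answers and explanations". Both arms get the same request for at least one hour. Participants know their arm (Randomization and blinding): "Although we cannot blind study personnel and participants to the intervention after allocation, we will mask group assignment during the analysis phase".

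**The concern.** The analysis rule and the assessment sequence pull in different directions. The rule wants physicians with little exposure kept. The sequence puts the simulation after completion of the task, so a physician who drops the app partway has not reached the point at which the article describes the log-in instruction. The group that the intention-to-treat rule is meant to protect is therefore the group most likely to have no outcome, and no analysis rule can recover an outcome that was never collected.

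Two things are at stake. First, completing the task is behaviour after randomisation, in an unblinded trial, on a task that differs by arm. If the two apps lose physicians at different rates, and those lost would have triaged differently, the comparison of tested physicians is biased. Second, the gap from last exposure to test can run from the same sitting to nearly a month. If that gap differs by arm, recency is mixed with the effect of the game. The ANOVA under Physician performance has no term for time since exposure.

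**Working it through.** **The plan's own figure.** A two-sample t-test with d = 0.5, two-sided alpha 0.05 (sidedness assumed) and 80% power needs 63.8, so 64 per group. Four cells give 4 × 64 = 256, and 256 / 0.70 = 365.7, so 366. The stated number reproduces on that reading. It implies 256 physicians with outcomes (128 per intervention arm) and 366 × 0.30 = about 110 without, if everyone who starts the intervention also finishes the simulation. The 70% is labelled a response rate, which the Analyses section defines as starting the intervention. The article gives no expected completion rate, so 30% outcome loss is an assumption below.

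**The passages side by side.**

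- Study protocol and Outcome assessment: the simulation follows completion of the intervention.
- Analyses: under one hour of use is no reason for exclusion; no simulation is.
- Together: the hour does not decide who is analysed, but it comes before the step that does.

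**Differential loss, simple model (all inputs assumed).** Let untested physicians differ from tested ones by g SD, in the same direction in both arms. Bias = (difference in completion) × g.

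- 70% vs 70%: 0 × g = 0.
- 65% vs 75%: 0.10 × 0.25 = 0.025 SD; 0.10 × 0.5 = 0.05 SD.
- 60% vs 80%: 0.20 × 0.25 = 0.05 SD; 0.20 × 0.5 = 0.10 SD.

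**Differential loss, selection model (all inputs assumed).** Let adherence be a latent normal variable with correlation rho to triage performance, let the lowest fraction p in each arm be lost, and let there be no true effect. The mean of those retained is rho × phi(z_p)/(1 − p), and the bias is the difference between arms. SE = sqrt(1/n1 + 1/n2) with 183 randomised per arm. Two-sided error = Phi(−1.96 + b/SE) + Phi(−1.96 − b/SE).

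| Losses | phi(z_p)/(1 − p) | SE | Bias, rho 0.3 to 0.5 | Two-sided error |
|---|---|---|---|---|
| 25% vs 35% | 0.424, 0.570 | 0.125 | 0.04 to 0.07 SD | 6.4% to 9.0% |
| 20% vs 40% | 0.350, 0.644 | 0.126 | 0.09 to 0.15 SD | 11% to 21% |
| 12.5% vs 17.5% (first row halved) | 0.235, 0.312 | 0.113 | 0.02 to 0.04 SD | 5.5% to 6.3% |
| 10% vs 20% (second row halved) | 0.195, 0.350 | 0.114 | 0.05 to 0.08 SD | 6.9% to 10.5% |

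The last two rows assume that inviting everyone recovers half of the losses. If less adherent physicians triage worse, the bias favours the arm that loses more.

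**Delay (inputs assumed).** If the effect halves every 28, 14 or 7 days, a test 7 days later keeps 0.5^(7/28) = 84%, 0.5^(7/14) = 71% or 0.5^(7/7) = 50% of it. Main-effect power with 128 per arm is Phi(d / sqrt(2/128) − 1.96), where sqrt(2/128) = 0.125. With d = 0.50 it is 98%. If delay weakens the effect by 10%, 20%, 30% or 50%, it is 95%, 89%, 80% or 52%.

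**The case against.** A reader might infer that a physician who stops early is never told to take the simulation, or is shut out of it. The article does not support that. Every physician gets written instructions for the whole protocol at enrolment, and the reminders concern a protocol described as having two portions. The Data security section issues the website identifier at enrolment. No technical gate is described. Wording such as after completing also states an order that any post-intervention test needs, and the plan to analyse physicians with under an hour of use shows that the authors expect some of them to be tested. The instruction sheet and emails are not shown, and an article need not print them. All of this stands, and it limits the point to a raised chance of missing outcomes.

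A reader might also infer that the arms will differ because the game is longer. That too is unsupported. Three hours of play is only possible, not required. The control is open-ended as well, with 550 questions besides chapter reviews and videos. The article calls the programs similar in duration, and the one-hour request, the window and the reminders are common to both arms.

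Finally, the error rates of 6% to 21% might be read as the size of the problem. They are not. They rest on assumed splits and correlations, and on treating a rate defined as starting the intervention as if it were outcome loss.

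What the objection does not remove is the published sequence and the open date. Self-paced completion is defensible for remote volunteers, but it does not require leaving partial users without an explicit prompt to be tested.

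**Conclusion.** The point holds as a design improvement, not as an error or contradiction that invalidates the plan. The sequence makes missing outcomes more likely among the low adherers whom the analysis means to keep, and nothing controls the interval from exposure to test. Whether either differs by arm is unknown before data. If losses are equal and relate to performance in the same way in both arms, these models give no bias. Under the assumed unequal losses, bias runs from 0.025 to 0.15 SD across the two models, against the 0.5 SD design effect. These figures illustrate the mechanism and do not estimate it. The common one-month limit and the shared reminders bound the problem. The change is worth making because it is cheap and serves the plan's own intention-to-treat aim.

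**What to change.** Keep the order of intervention, then simulation. Under Study protocol and Outcome assessment, add:

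- In the final week of the one-month window, every randomised physician in either arm who has not taken the simulation receives the same invitation to take it, whatever their logged app use.
- Physicians who finish the intervention are asked, in the same words in both arms, to take the simulation promptly after their last session.
- Days from last logged app use to simulation are reported by arm.

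The cost is a changed instruction sheet and one added or changed email. App use is already logged and downloaded daily (Data sources and management), and the sample size does not change. Finishers still choose their own date, so the interval is reported and shortened rather than fixed.

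There are three downsides. More low-exposure physicians enter the analysis, which slightly dilutes the effect; the Analyses section already accepts this. An invitation that ignores app use could tempt some to skip the intervention, which is why it is held to the last week. The article gives the trial status as recruiting, so if enrolment has begun, the date of the change must be recorded.
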